## Abstract

**Background:**

The ideal long-term antithrombotic strategy for patients after successful catheter-based atrial fibrillation (AF) ablation is still uncertain. Presently, practices vary, and the advantages of oral anticoagulation (OAC) for the post-ablation population are not clearly established. To date, no randomized trials have addressed this therapeutic question. This study aimed to evaluate whether no OAC therapy is superior to apixaban in reducing the risk of stroke, systemic embolism, or major bleeding among patients without apparent recurrent atrial arrhythmias for at least 1 year after their AF ablation procedure.

**Methods:**

The ALONE-AF trial is a prospective, multicenter, open-label, randomized study with blinded outcome assessment. Patients with AF who have at least one non-gender stroke risk factor (as determined by the CHA_2_DS_2_-VASc score) and no documented recurrences of atrial arrhythmia for at least 12 months post-ablation will be randomly assigned to apixaban 5 mg b.i.d. or no OAC therapy. The primary endpoint is a composite outcome of stroke, systemic embolism, and major bleeding. Key secondary outcomes include clinically relevant non-major bleeding, all-cause mortality, myocardial infarction, transient ischemic attack, quality of life, and frailty analysis. Participants will be followed for a period of 2 years. The estimated total sample size is 840 subjects, with 420 subjects in each arm.

**Conclusion:**

The ALONE-AF trial aims to provide robust evidence for the optimal anticoagulation strategy for patients with stroke risk factors following successful AF ablation.

**Clinical Trial Registration**: NCT04432220 (https://www.clinicaltrials.gov)

## Background

1

Atrial fibrillation (AF) stands as the most prevalent form of sustained cardiac arrhythmia, imposing substantial economic and public health burdens [[1], [2], [3], [4]]. Compared to pharmacological therapy, AF catheter ablation (AFCA) has demonstrated efficacy in reducing acute episodes and prolonging periods of sinus rhythm, thereby enhancing patients' quality of life [1,2,5,6]. However, uncertainty persists regarding the impact of AFCA on the incidence of thromboembolic events [7,8]. While contemporary guidelines generally advocate for continuing oral anticoagulants (OACs) following successful AFCA, the long-term effects of OAC continuation on thrombotic and bleeding complications remain inadequately evaluated in randomized trials [1,2,6]. Earlier observational studies, primarily focusing on warfarin-treated patients, have hinted at a potential reduction in thromboembolic risk with ongoing OAC therapy post-AFCA, albeit with an associated heightened risk of serious bleeding. Observational evidence hints that discontinuing OACs after AFCA may result in a low annual thromboembolic complication rate [[9], [10], [11], [12], [13], [14], [15], [16], [17], [18], [19]]; however, caution is warranted due to study limitations. Further research is needed to guide optimal long-term antithrombotic management post-AF ablation.

The AnticoaguLation ONE year after Ablation of Atrial Fibrillation in Patients with Atrial Fibrillation (ALONE-AF trial; NCT04432220) is a multicenter, randomized controlled study focused on determining the best stroke prevention approach for patients at risk following AF ablation, as indicated by their CHA_2_DS_2_-VASc score [20]. For patients who have not experienced atrial arrhythmia recurrences for at least 12 months after AF ablation, the study hypothesizes that discontinuing OAC therapy will lower the risk of adverse outcomes, such as stroke, systemic embolism, and major bleeding, compared to using direct oral anticoagulants (DOACs).

## Methods

2

### Study design

2.1

The ALONE-AF trial represents a multicenter, open-label, prospective, randomized superiority trial designed to enroll participants at risk for stroke who have not had any recurrences of atrial arrhythmia for at least 12 months following AF ablation. The study's overall flowchart is depicted in Fig. 1. The study protocol received approval from the institutional review board of each participating center, and patient enrollment commenced in July 2020.

**Fig. 1 fig1:**
[figure not shown]
Flow chart of the ALONE-AF trial.

### Study participants and enrollment criteria

2.2

All patients with non-valvular AF undergoing their first AFCA procedure will be screened for eligibility. To be eligible for enrollment, patients must meet the following three criteria: 1) age between 19 and 80 years; 2) a CHA_2_DS_2_-VASc score of at least 1 for men or 2 for women; and 3) no atrial arrhythmia recurrence for at least 12 months post-AF ablation, defined as the absence of ≥30 s of atrial fibrillation (AF), atrial flutter (AFL), or atrial tachycardia (AT) in at least two 24–72 h Holter and electrocardiogram (ECG) recordings conducted beyond 3 months after the ablation and before enrollment (requiring at least one 24–72 h Holter monitor and ECG recording within the 2 months prior to enrollment). Patients will be enrolled regardless of the lesion set or energy source used for AF ablation. Key exclusion criteria include: 1) significant renal or liver disease; 2) requirement for anticoagulation for reasons other than AF (such as moderate-to-severe mitral valve stenosis, the presence of a mechanical heart valve, or a history of deep vein thrombosis); and 3) significant structural heart disease. Detailed information on the inclusion and exclusion criteria is presented in Table 1. Written informed consent will be obtained from each subject prior to enrollment.

**Table 1 tbl1:** Inclusion and exclusion criteria.

Inclusion criteria
1. Age between 19 and 80 years
2. CHA_2_DS_2_-VASc score ≥1 (male) or ≥ 2 (female)
3. No recurrence of atrial arrhythmia at least 12 months after their first-time catheter ablation of atrial fibrillation, defined as an absence of ≥30 s of atrial fibrillation, atrial flutter, or atrial tachycardia in at least two 24–72 h Holter and electrocardiogram recordings conducted beyond 3 months after the ablation and before enrollment (with at least one 24–72 h Holter and electrocardiogram recording mandatory within the 2 months preceding enrollment)
**Exclusion criteria**
1. Significant liver (aspartate transaminase and/or alanine transaminase >3 times the upper limit of normal) or renal disease (serum creatinine ≥3.5 mg/dl or creatinine clearance <30 ml/min)
2. Requiring anticoagulation due to surgery with a mechanical prosthetic valve, moderate-to-severe mitral stenosis, or deep vein thrombosis
3. Significant structural heart disease (moderate-to-severe mitral regurgitation, severe valvular regurgitation or stenosis, dilated cardiomyopathy, or hypertrophic cardiomyopathy)
4. Active malignancy
5. Pregnancy or breast-feeding
6. Life expectancy <1 year
7. Refuse or enable to understand the written informed consent

### Randomization and study procedures

2.3

Eligible patients will be randomized to receive OAC therapy or no OAC therapy in a 1:1 ratio. Randomization will be conducted using a web-response permuted-block method at each participating center. Participants allocated to the OAC therapy group will receive apixaban at a dose of 5 mg twice daily. The apixaban dose will be reduced to 2.5 mg twice daily for patients who meet at least two of the following conditions: 1) age 80 years or older, 2) body weight 60 kg or less, and 3) serum creatinine level above 1.5 mg/dL [21]. In cases where a subject experiences intolerable adverse effects with apixaban, an alternative DOAC may be prescribed. Subjects assigned to the no OAC therapy group will not receive any oral anticoagulant. However, antiplatelet therapy may be administered if clinically indicated (e.g., for percutaneous coronary intervention or acute coronary syndrome) in both groups. All patients underwent ECG at each visit and 24- to 72-h Holter monitoring at least every six months after enrollment. Additionally, Holter monitoring or event recordings were conducted whenever patients reported symptoms of palpitations suggestive of arrhythmia recurrence. If a patient experiences a documented recurrence of atrial arrhythmia or undergoes repeat AFCA during the study period, they will be censored at that point and prescribed anticoagulation based on the patient's stroke risk or periprocedural needs. Subjects will be followed up for a maximal duration of 24 months.

### Study outcomes

2.4

The primary outcome, assessed at the 2-year mark following randomization, is a composite endpoint comprising stroke, systemic embolism, and major bleeding (see Table 2). Stroke is defined as a sudden, focal neurologic deficit resulting from a presumed cerebrovascular cause that persists for more than 24 h and is not attributable to a readily identifiable cause, such as a tumor or seizure [22]. Systemic embolism is defined as abrupt vascular insufficiency accompanied by clinical or radiological evidence of arterial occlusion, occurring in the absence of other likely mechanisms (e.g., trauma, atherosclerosis, or instrumentation). Major bleeding events will be defined according to established criteria [22]. Major bleeding was defined by the International Society on Thrombosis and Hemostasis (ISTH) criteria [23].

**Table 2 tbl2:** Study outcomes.

Primary outcome
A composite of stroke, systemic embolism, and major bleeding (defined by the ISTH criteria)

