**Secondary outcome**
Stroke
Systemic embolism
ISTH major bleeding
ISTH clinically relevant non-major bleeding
All-cause death
Myocardial infarction
Pulmonary thromboembolism
Hospitalization
AFQET
K-MoCA
Frailty (Questionnaire and grip strength)

AFQET, Atrial Fibrillation Effect on QualiTy-of-Life; ISTH, International Society on Thrombosis and Hemostasis; K-MoCA, Korean version of Montreal Cognitive Assessment.

Secondary outcomes of the study will include the individual components of the primary outcome, namely stroke, systemic embolism, and major bleeding events. Additionally, we will evaluate the incidence of clinically relevant nonmajor bleeding, as defined by the ISTH criteria [24]. Additional secondary outcomes encompass all-cause mortality, myocardial infarction (MI), pulmonary thromboembolism (PTE), transient ischemic attack (TIA), and hospitalization due to any cause. The definitions of MI and PTE are presented in Supplement. TIA will be defined as the presence of a new focal neurologic deficit presumed to be vascular in origin, with signs or symptoms lasting less than 24 h, without evidence of infarction as assessed by brain imaging [25]. The Atrial Fibrillation Effect on QualiTy-of-life (AFEQT) [26], frailty assessments (including questionnaires and grip strength measurement), and the Korean-Montreal Cognitive Assessment will be evaluated at baseline, as well as at the 1-year and 2-year follow-up time points. Adjudication of study outcomes will be performed by an independent clinical event adjudication committee, which will remain blinded to the primary results of the study.

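### As defined, a focal deficit of under 24 h with infarction on brain imaging is neither stroke nor TIA, so it is lost from the primary composite and from both of those outcomes

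*Protocol article*

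**What the plan says.** All of this is in the protocol article, section 2.4 (Study outcomes), unless stated.

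- **Stroke** is a sudden focal deficit "resulting from a presumed cerebrovascular cause that persists for more than" 24 h and not due to another identifiable cause. Duration is the only threshold; no imaging route is offered.
- **TIA** is a new focal deficit of presumed vascular origin "with signs or symptoms lasting less than 24 h, without evidence of infarction as assessed by brain imaging".
- **Systemic embolism** is "abrupt vascular insufficiency accompanied by clinical or radiological evidence of arterial occlusion", without other likely mechanisms. Brain infarction is not mentioned.
- **The primary outcome** combines stroke, systemic embolism and ISTH major bleeding. Death is not a component.
- **Secondary outcomes** in the text include all-cause mortality, "transient ischemic attack (TIA), and hospitalization due to any cause". The Abstract also names TIA as a key secondary outcome. Table 2 does not list it.

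Only the definitions of MI and pulmonary thromboembolism are sent to the Supplement. Stroke and TIA are worded in the article itself. A blinded independent committee adjudicates.

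**The concern.** The two definitions rest on different principles. Stroke is defined by time alone, TIA by time and tissue. The TIA wording pushes infarct-positive events out, but the stroke wording does not take them in. A short-lived deficit without infarction is counted as TIA, while the same deficit with a proven infarct is counted as neither.

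This matters because the trial sets thromboembolic events against bleeding in one composite and asks whether no OAC is superior. Section 2.5 expects the benefit to come from fewer major bleeds, so ischaemic events are the counterweight. The 24 h rule acts on that side only, since no such rule is stated for major bleeding. Any loss of ischaemic events that differs by arm would carry into both the composite and the stroke component.

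**Working it through.** **Step 1. Cross duration with imaging.** Applying the wording literally:

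| Deficit | Infarct on imaging | No infarct on imaging |
|---|---|---|
| More than 24 h | Stroke | Stroke |
| Exactly 24 h | Neither | Neither |
| Less than 24 h | **Neither** | TIA |
| Fatal before 24 h | Not stroke; counted as death | Not stroke; counted as death |

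The systemic embolism definition does not name brain infarction, so it does not clearly fill the empty cell. Any-cause hospitalization may catch the patient but does not identify the event as ischaemic. A fatal haemorrhagic event might also qualify as major bleeding, but the article cites those criteria without reproducing them.

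**Step 2. The plan's own figure.** Inputs from section 2.5: 9.2% with OAC over 2 years, an absolute reduction of 5.0 points (so 4.2% without OAC), two-sided 5% alpha, 80% power, 7% dropout.

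n per arm = [1.960 × √(2 × 0.067 × 0.933) + 0.842 × √(0.092 × 0.908 + 0.042 × 0.958)]² / 0.05² = 392.

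Dropout as 392 × 1.07 gives 420 per arm (840 in total); as 392 / 0.93 it gives 422 (844). The stated 840 reproduces, and this point does not call it into question.

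**Step 3. Possible number of events.** Section 2.5 gives 1.0% per year for stroke and systemic embolism together, as part of the OAC-arm rate. Carrying it to both arms is an assumption, as is using all 420 patients without dropout or censoring.

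- Expected events per arm: 420 × 0.02 = 8.4.
- Share with infarction and symptoms under 24 h: not in the document. ASSUMED 10–20%.
- Events affected: 8.4 × 0.10 = 0.8 to 8.4 × 0.20 = 1.7 per arm.
- One event is 1/420 = 0.24 points, so this is about 0.2 to 0.4 points per arm.

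**Step 4. Effect on the comparison.** Power with 390 evaluable per arm, after adding the uncounted events back. All added rates are assumed.

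| Added with OAC | Added without OAC | Rates compared | Difference | Power |
|---|---|---|---|---|
| 0 | 0 | 9.2% v 4.2% | 5.0 points | 79.9% |
| 0.2 points | 0.2 points | 9.4% v 4.4% | 5.0 points | 78.8% |
| 0.4 points | 0.4 points | 9.6% v 4.6% | 5.0 points | 77.7% |
| 0.1 points | 0.4 points | 9.3% v 4.6% | 4.7 points | 73.4% |

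Equal frequency leaves the risk difference unchanged and costs little power. Unequal frequency changes it: in the last row, leaving the events out would overstate the benefit of no OAC by 0.3 points.

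**The case against.** A duration-based stroke definition with a cited source is a legitimate choice, and an adjudication charter that is not shown may settle boundary cases. Both points are fair, but they do not fill the empty cell. The article words both definitions itself, and nothing in it lets the committee call a deficit of under 24 h a stroke. If the charter already assigns these events, only the article needs correcting.

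Several stronger readings are tempting and are not supported:

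- *That confirmed cerebral infarctions in general go uncounted.* Those with deficits beyond 24 h count as stroke. Some of the rest may appear as hospitalization or death.
- *That the omission does favour no OAC.* This holds only if short-lived infarctions are more frequent without OAC, which is part of what the trial tests. The Discussion cites one observational study linking discontinuation to more cardioembolism in high-risk patients and another finding no increase in thromboembolism.
- *That two or three events would be lost in the no-OAC arm.* This needs a stroke risk of about 4% there (420 × 0.04 = 16.8; 10–20% of that is 1.7 to 3.4). Section 2.5 implies 4.2% for the whole composite in that arm, leaving 0.2% for major bleeding over 2 years.

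One objection stands against any imaging-based criterion. The trial is open-label and the article does not mandate imaging of transient deficits. If clinicians who know the arm decide who is scanned, blinded adjudication cannot recover scans that were never ordered.

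**Conclusion.** The gap is real and follows from the two definitions as written. A deficit of under 24 h with imaging-proven infarction is lost from the primary composite and from the stroke and TIA outcomes. A stroke fatal within 24 h fails the duration rule and is left to all-cause death. A deficit of exactly 24 h is also unassigned.

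The size cannot be quantified from the document. About 1–2 events per arm is an illustration that rests on an assumed 10–20% share and on the same 2% two-year risk in both arms. The direction of any bias is conditional on an ischaemic excess without OAC. The point is worth correcting because the rule misclassifies the more serious event and the correction is cheap, not because a large effect has been shown. The absence of TIA from Table 2 is editorial and adds no weight.

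**What to change.** Make the definitions exhaustive and non-overlapping:

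- **Stroke:** an acute focal deficit of presumed vascular cause that lasts at least 24 h, or ends in death before 24 h, or lasts less than 24 h with matching infarction or haemorrhage on imaging.
- **TIA:** such a deficit lasting less than 24 h without that imaging evidence.

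Do not add reperfusion treatment as a further route to stroke unless those cases are explicitly excluded from TIA. Otherwise a treated patient who recovers within 24 h without infarction would meet both definitions.

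Have the blinded committee re-check transient and early-fatal events under this wording, using imaging already obtained, before arm-level results are seen. Report the primary endpoint under the current duration-only definition as a sensitivity analysis. Report by arm how many transient deficits were imaged, so that readers can judge whether ascertainment differed. Add TIA to Table 2.

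The cost is a re-review of what should be few events and a change of wording in the protocol and in any adjudication charter. Because enrolment began in July 2020, this is a change to a component of the primary endpoint during the trial. It must be dated, justified and documented as such. Reclassification will also remain limited to patients who happened to be imaged.

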**Secondary outcome**
Stroke
Systemic embolism
ISTH major bleeding
ISTH clinically relevant non-major bleeding
All-cause death
Myocardial infarction
Pulmonary thromboembolism
Hospitalization
AFQET
K-MoCA
Frailty (Questionnaire and grip strength)

AFQET, Atrial Fibrillation Effect on QualiTy-of-Life; ISTH, International Society on Thrombosis and Hemostasis; K-MoCA, Korean version of Montreal Cognitive Assessment.

Secondary outcomes of the study will include the individual components of the primary outcome, namely stroke, systemic embolism, and major bleeding events. Additionally, we will evaluate the incidence of clinically relevant nonmajor bleeding, as defined by the ISTH criteria [24]. Additional secondary outcomes encompass all-cause mortality, myocardial infarction (MI), pulmonary thromboembolism (PTE), transient ischemic attack (TIA), and hospitalization due to any cause. The definitions of MI and PTE are presented in Supplement. TIA will be defined as the presence of a new focal neurologic deficit presumed to be vascular in origin, with signs or symptoms lasting less than 24 h, without evidence of infarction as assessed by brain imaging [25]. The Atrial Fibrillation Effect on QualiTy-of-life (AFEQT) [26], frailty assessments (including questionnaires and grip strength measurement), and the Korean-Montreal Cognitive Assessment will be evaluated at baseline, as well as at the 1-year and 2-year follow-up time points. Adjudication of study outcomes will be performed by an independent clinical event adjudication committee, which will remain blinded to the primary results of the study.

### Sample size estimation

2.5

Based on the assumptions provided, including an annual primary outcome rate of 4.6 % in the OAC therapy group (comprising a 1.0 % annual stroke/systemic embolism rate after AFCA and a 3.6 % annual major bleeding rate observed in a pivotal randomized trial of DOAC) [[27], [28], [29]], the total expected primary outcome rate over 2 years was estimated as 9.2 %. This study aims to show that no OAC therapy will achieve a 5.0 % absolute risk reduction over 2 years (equivalent to a 54 % relative risk reduction driven by the reduction of major bleeding) compared with OAC therapy [29,30]. Considering an anticipated 7 % dropout, and aiming for 80 % power and a 5 % two-sided alpha error, a total of 840 patients will be required, with 420 patients allocated to each arm of the trial.

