### Statistical analyses

2.7

Continuous variables will be expressed as means ± standard deviations or medians with interquartile ranges, depending on the distribution. Categorical variables will be displayed as frequencies and percentages. For comparisons, the Student's t-test or Mann-Whitney *U* test will be employed for continuous variables, while the chi-square test or Fisher's exact test will be utilized for categorical variables, as suitable.

The primary analyses will be performed on the intention-to-treat (ITT) population. For the primary objective, the cumulative event rate during clinical follow-up will be estimated using the Kaplan-Meier method, with a 95 % confidence interval calculated for the difference in event rates. As a sensitivity analysis, the primary endpoint analysis will also be performed on the per-protocol (PP) population. The ITT population will include all randomized patients, compared according to their assigned group regardless of the treatment actually given. The PP population will exclude patients with protocol deviations, including those found to be ineligible, those without informed consent, or those for whom the randomized therapy was not implemented. For secondary endpoints, the incidence or cumulative incidences of each endpoint will be calculated using Kaplan-Meier plots for comparisons. Missing variables will not be imputed for planned analyses, except where specified otherwise. Patients with missing values will be excluded from variable-related analyses but included in analyses not related to the missing variable. Patients lost to follow-up and subsequently lost to assessment of the primary endpoint will be considered censored in the estimation of Kaplan-Meier event rates There is no planned formal interim analysis or guidelines for stopping the study. However, the data and safety monitoring board (DSMB) will review safety data in a blinded manner, with the DSMB statistician providing unblinded summary tables. The DSMB will discuss and determine whether early termination is required due to safety concerns.

Subgroup analyses will be conducted to compare the hazard ratio (HR) of no OAC therapy against OAC therapy, stratified by prespecified subgroups including age (<65 vs. ≥65 years), sex (male vs. female), diabetes (Yes vs. No), hypertension (Yes vs. No), heart failure (Yes vs. No), vascular disease (Yes vs. No), AF type (paroxysmal vs. non-paroxysmal), and time from diagnosis to ablation (<1 year vs. ≥1 year).

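### The sample size allows for 7% dropout but not for censoring at recurrence, so the stated 80% power depends on a recurrence rate that the protocol does not give

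*Protocol article*

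**What the plan says.** Section 2.5 (Sample size estimation) starts from "an annual primary outcome rate of 4.6 % in the OAC therapy group", made up of 1.0% stroke or systemic embolism and 3.6% major bleeding. It doubles this: "the total expected primary outcome rate over 2 years was estimated as" 9.2%. The aim is that "no OAC therapy will achieve a 5.0 % absolute risk reduction over 2 years", described as "equivalent to a 54 % relative risk reduction driven by the reduction of major bleeding". The only allowance for lost information is "Considering an anticipated 7 % dropout". With 80% power and two-sided 5% alpha, this leads to 420 patients per arm.

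Section 2.3 (Randomization and study procedures) says of patients with a documented atrial arrhythmia recurrence or a repeat ablation that "they will be censored at that point". It requires Holter monitoring at least every six months, so recurrence is actively looked for.

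Section 2.7 (Statistical analyses) says that for the primary objective "the cumulative event rate during clinical follow-up will be estimated using the Kaplan-Meier method", with a 95% confidence interval for the difference. Loss to follow-up is a further reason for censoring there.

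**The concern.** Follow-up can end early for two reasons, dropout and recurrence (or repeat ablation), and Section 2.5 makes room for only the first. Section 2.5 lists its inputs, and recurrence is not among them. The plan has no power in reserve, so any further loss of follow-up takes it below 80% unless something else offsets it.

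A second, smaller point lies in the same paragraph. Doubling an annual rate overstates a 2-year cumulative risk, which is what Kaplan-Meier estimates. The paragraph treats 5.0 points and 54% as one target. Once the 2-year risk is made consistent with the annual rate they separate, and the power depends on which is meant.

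At stake is how a null result would be read. In a superiority trial it is judged against the stated power, here a single 80% that rests on more follow-up than the design will deliver.

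**Working it through.** **Inputs from the protocol.** Annual rate 4.6%; 2-year risks 9.2% and 9.2 − 5.0 = 4.2%; 7% dropout; 80% power; two-sided 5%; 420 per arm; 24 months of follow-up. **Not in the protocol:** the share of patients with recurrence or repeat ablation over 2 years. I vary it from 0 to 30% as an assumption.

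**1. Reproduce 840.** The mean risk is 0.067.

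n = [1.96·√(2·0.067·0.933) + 0.8416·√(0.092·0.908 + 0.042·0.958)]² / 0.05² = (0.6930 + 0.2961)² / 0.0025 ≈ 391.3, so 392 per arm.

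Inflation for 7% gives 392 × 1.07 = 419.4 (420), or 392 / 0.93 = 421.5 (422). The plan's 420 is reproduced. Read the other way, 420 × 0.93 = 390.6 evaluable per arm gives 79.9% power.

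**2. Power of the Kaplan-Meier difference.** Take constant event hazard λ = −ln(1 − p)/2 and constant censoring hazard c, the same in both arms and unrelated to prognosis. The large-sample Greenwood variance at 2 years is

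Var = (1 − p)² · [λ/(λ + c)] · [exp(2(λ + c)) − 1] / n,

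and power = Φ(difference/SE − 1.96). Dropout is handled in two ways: all lost at the start (n = 390.6), or spread through follow-up (n = 420, with −ln(0.93)/2 added to c). The first gives the lower end of each range below.

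Example: 9.2% vs 4.2%, 20% recurrence, dropout spread through follow-up. c = [−ln(0.80) − ln(0.93)]/2 = 0.1479; λ = 0.0483 and 0.0215. The variances are 0.000232 and 0.000112, SE = 0.01854, and power = Φ(0.05/0.01854 − 1.96) = 77.0%.

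**3. Two-year risks that follow from the annual rates.** The 54% reduction takes 4.6% to 2.1% per year.

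- As hazards: 1 − exp(−0.092) = 8.8% and 1 − exp(−0.042) = 4.1%, a difference of 4.7 points.
- As annual risks, compounded: 1 − 0.954² = 9.0% and 1 − 0.979² = 4.2%, a difference of 4.8 points.
- With 5.0 points held at 8.8%: 8.8% vs 3.8%, a relative reduction of 5.0/8.8 = 57%.

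**4. Power (%) by assumed 2-year recurrence, 420 per arm, 7% dropout.**

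| Recurrence | 9.2 vs 4.2 (as stated) | 8.8 vs 4.1 (54% held, hazard) | 9.0 vs 4.2 (54% held, compounded) | 8.8 vs 3.8 (5.0 points held) |
|---|---|---|---|---|
| 0% | 80.2-81.6 | 76.2-77.7 | 78.2-79.6 | 82.5-83.8 |
| 10% | 78.1-79.5 | 73.9-75.4 | 76.0-77.4 | 80.4-81.8 |
| 20% | 75.5-77.0 | 71.3-72.8 | 73.4-74.9 | 78.0-79.4 |
| 30% | 72.6-74.0 | 68.3-69.7 | 70.4-71.8 | 75.1-76.5 |

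On the stated risks, power drops below 80% once recurrence passes about 1% (dropout at the start) or about 8% (dropout spread). With 5.0 points held at 8.8%, it does so at about 12% and 18%. With 54% held, it is below 80% with no recurrence at all.

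**The case against.** **The plan contains no calculation error.** This stands. From its own inputs 840 is right, and a reader who inferred that the sample size was miscalculated would be mistaken.

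**No single lower power can be read off the protocol.** This also stands. A reader might infer that the true power is about 73-76%. That figure needs both an assumed recurrence share and the choice to hold 54% fixed. If the 5.0 points that Section 2.5 states as the aim is held instead, correcting the 2-year risk raises power before recurrence. Over 0-30% recurrence the readings in the table run from 68% to 84%, which includes 80%.

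**Kaplan-Meier is not to blame.** Correct: with the stated risks and 7% dropout alone it gives 80-82%. The loss comes from the extra censoring. A log-rank comparison would be more forgiving, with about 79-81% on the stated risks at 20% recurrence, but Section 2.7 names the Kaplan-Meier difference for the primary objective.

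**Adding the component rates counts some patients twice.** A reader might make something of this, but under independence the overlap is about 2.0% × 7.2% = 0.14 points over 2 years, and the protocol does not show how the source rates were counted. It is too small to press.

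**Censoring at recurrence may not govern the primary analysis.** Section 2.7 specifies intention to treat and mentions only patients lost to follow-up as censored. That leaves some doubt, but the rule in Section 2.3 carries no exception for the primary analysis. If events after recurrence were counted, this loss of information would not arise and a different power calculation would be needed.

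**Conclusion.** The point holds in a conditional form. Section 2.5 allows for one of two planned sources of lost follow-up and has no power in reserve. Granting every stated input, power is about 80-82%, 78-80%, 76-77% and 73-74% at assumed 2-year recurrence of 0, 10, 20 and 30%. The protocol gives no recurrence rate, so it does not establish where in that range the trial lies.

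The doubling of the annual rate is a lesser inconsistency whose direction depends on the target. Before recurrence, power is 76-78% (hazard) or 78-80% (compounded) if 54% is held, and 82-84% if 5.0 points is held at 8.8%. It shows that the two targets are not exactly equivalent; it does not by itself show that the trial is underpowered.

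All figures assume constant hazards and censoring that is equal between arms and unrelated to outcome.

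**What to change.** Keep N at 840 and revise Section 2.5 in three places:

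- Say whether 5.0 points or 54% is the target effect, and give 2-year risks for both arms that agree with the annual rates.
- Beside the 7% dropout, state an assumed share censored for recurrence or repeat ablation, with its basis.
- Replace the single 80% with the power of the planned Kaplan-Meier difference over a range of recurrence, for example 0-30%.

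If events after recurrence are in fact to count in the intention-to-treat analysis, Sections 2.3 and 2.7 should say so, and the power should be worked out for that case separately.

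The cost is wording and, on most readings, a slightly less favourable stated power. No patients are added, and the analysis does not change.
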